#### Methods in analysis to handle protocol non-adherence and any statistical methods to handle missing data {20c}

The number of subjects with missing data by reason will be examined for each randomisation group (and for each outcome). Characteristics of participants with and without missing outcome data will be compared using logistic regression models (with missing yes/no as the outcome) and characteristics that predict missingness identified. In a sensitivity analysis, the treatment effect will then be re-estimated with additional adjustment for baseline predictors of missingness. Further analyses based on multiple imputation methods will be considered if appropriate. Analyses will be carried out based on the intention to treat principle.

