### Outcomes {12}

All outcomes will be collected at baseline and 6 and 12 months.

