### Data collection and management

#### Plans for assessment and collection of outcomes {18a}

Data is collected at baseline and 6- and 12-month follow-up for all participants (Table 1). Those in the intervention group are asked to complete an additional measure on acceptability of the intervention at the end of the study. Approximately 10% of participants in the intervention group will participate in an additional qualitative interview about their experiences of receiving the intervention. All researchers are fully trained to use the data collection tools. All outcome assessments will be measured using validated questionnaires (please refer to the ‘Objectives’ section of this protocol for a list of validated questionnaires that will be used in this trial).

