#### Primary outcome analysis

Family carer-rated Goal Attainment Scaling (GAS) global mean scores at 12 month follow-up will be summarised for the NIDUS-family and usual care groups using means with standard deviations. The outcome will be compared between the groups using a three level mixed effects model which allows for intervention arm therapist clustering and also includes a random effect for study site. The treatment effect estimate from this model will be the adjusted difference in mean GAS score which will be reported with a 95% confidence interval and *P* value. Analyses will be carried out based on the intention to treat principle, comparing the groups as randomised regardless of adherence to the intervention.

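### The primary model uses 12-month goal attainment only, and the one committed missing-data analysis adjusts for baseline predictors, leaving the scheduled 6-month ratings without a stated use in estimating the effect

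*Protocol article*

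**What the plan says.** **Collection.** Under Outcomes {12}: "All outcomes will be collected at baseline and 6 and 12 months". Under Plans for assessment and collection of outcomes {18a}: "Data is collected at baseline and 6- and 12-month follow-up for all participants". Table 1 marks GAS and the clinical scales at baseline, t9 (6 months) and t14 (12 months).

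**Primary analysis.** The summary is of the final wave: "Family carer-rated Goal Attainment Scaling (GAS) global mean scores at 12 month follow-up will be summarised". The comparison uses a "three level mixed effects model which allows for intervention arm therapist clustering and also includes a random effect for study site". No time or repeated-measures term is mentioned, and the 6-month rating does not enter. The section on secondary outcomes takes a similar approach for the continuous scores and adds the baseline value of each.

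**Missing data, section {20c}.** Baseline characteristics that predict missingness are to be identified, and then, as a sensitivity analysis, "the treatment effect will then be re-estimated with additional adjustment for baseline predictors of missingness". The next sentence reads: "Further analyses based on multiple imputation methods will be considered if appropriate". It does not say what would trigger imputation or what the imputation model would contain.

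**Detail.** The opening of Statistical methods leaves detail to a separate analysis plan, which is not shown.

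**The concern.** As described, a dyad rated at 6 months but not at 12 adds nothing to the primary estimate, although its early progress is known. The 12-month-only model is unbiased if, within each arm, being missing is unrelated to the 12-month score, or if the relation is the same in both arms. Baseline adjustment relaxes this only for what was measurable before randomisation. GAS rates progress on goals set at baseline, so a baseline covariate cannot stand in for attainment. The 6-month rating is the only scheduled earlier measure of it.

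Dropout that differs by arm is plausible in this design. Participants know their allocation (section {17a}). Intervention dyads receive calls every one to two months in the second half-year (section {11a}), while control dyads have no such contact from the trial. Dyads in the two arms could therefore leave for different reasons. The documents do not show that this will happen; they leave it possible.

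At stake is the size of the primary effect, and likewise the continuous secondary outcomes, which share the approach.

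**Working it through.** **1. The plan's own figure.** The sample size section gives 198 intervention and 99 control dyads: effect 0.5 SD, two-sided 5%, 90% power, ICC 0.05 with average cluster size 20 in the intervention arm, up to 15% loss.

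- Design effect: 1 + (20 − 1) × 0.05 = 1.95.
- Control n before loss: (1 + 1.95/2) × ((1.96 + 1.28)/0.5)² = 83.0, using unrounded normal quantiles.
- After loss: 83.0/0.85 = 97.7, so 98 control, 196 intervention, 294 in total.
- With the noncentral t distribution, 98 controls give 89.9% power and 99 give 90.2%, so 99 and 198 are reproduced.

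The sample size is not in dispute. It supplies the 15% and the 0.5 SD used below: 0.15 × 297 ≈ 45 dyads lost, about 252 left.

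**2. Bias by formula.** Let p be the share missing at 12 months, g how far leavers lie below stayers at 6 months (in SD), and r the 6-to-12-month correlation. If dropout depends on the 6-month score, leavers would be about r × g lower at 12 months, and the observed arm mean is too high by p × r × g.

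- p = 0.15 is the plan's ceiling. The ranges r = 0.5 to 0.7 and g = 0.3 to 0.8 are assumptions; the documents give neither.
- Low corner: 0.15 × 0.5 × 0.3 = 0.0225 SD (4.5% of 0.5).
- High corner: 0.15 × 0.7 × 0.8 = 0.084 SD (17% of 0.5).

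For the between-arm difference the bias is r × (p_I × g_I − p_C × g_C), where I is intervention and C is control. It is zero when p × g is equal in the two arms. Poor progressors leaving only from control shrink the effect; poor progressors leaving only from intervention inflate it.

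**3. Check by simulation.** Assumptions: true 12-month effect 0.50 SD; 6-month effect 0.35 SD; 15% missing per arm; where dropout depends on the 6-month score, a log-odds slope of 1 per SD; everyone rated at 6 months; no therapist clustering; r = 0.3, 0.5 or 0.7.

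| Dropout depends on 6-month score | 12-month-only estimate | Using 6-month score |
|---|---|---|
| Equally in both arms | 0.50 | 0.50 |
| Control only, low scorers leave | 0.41 to 0.46 | 0.50 |
| Intervention only, low scorers leave | 0.54 to 0.59 | 0.50 |
| Opposite directions (high scorers leave intervention, low scorers leave control) | 0.31 to 0.42 | 0.50 |

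At r = 0.5 the one-arm bias is 0.066, which implies g = 0.066/(0.15 × 0.5) ≈ 0.9 SD. That is just above the range in step 2, so the two calculations agree. The last row is an extreme case.

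**4. Precision.** If a share s of those missing at 12 months were rated at 6 months, the variance of an arm mean is proportional to (1 − r²)/0.85 + r²/(0.85 + 0.15s).

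- s = 1, r = 0.7: 0.51/0.85 + 0.49/1 = 1.09. The effective N is 297/1.09 = 272.5 and the standard error falls by 3.8%.
- s = 0.25, r = 0.3: 0.91/0.85 + 0.09/0.8875 = 1.172. The effective N is 253.4 and the standard error falls by 0.2%.

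Precision is not the argument; protection against bias is.

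**The case against.** - **Imputation is mentioned.** A reader might infer that missing data are handled only with baseline predictors. The text does not support that: the sentence after the committed analysis allows multiple imputation, which could include 6-month GAS. What stands is that this option is conditional and unspecified and would leave the primary model as it is.
- **Detail belongs to the unseen analysis plan.** True of imputation settings. But the article itself states the primary model and the committed sensitivity analysis, and the point is about those stated choices.
- **Restricting covariates to baseline is correct.** It is. Putting 6-month GAS into the treatment-effect model as a covariate would condition on a consequence of treatment. This governs how the 6-month score is used; it does not bar a joint model or its use as an auxiliary variable in imputation.
- **Intention to treat.** A reader might infer that the analysis is not intention to treat as claimed. The article defines the principle as comparing groups as randomised whatever their adherence, and the model does so. Missing outcomes are a separate matter.
- **The 6-month wave.** A reader might infer that it serves no purpose. The economic evaluation takes QALYs as an area under the curve from DEMQOL, which is collected at 6 months. The narrower statement stands: the article gives the wave no role in estimating clinical effects.
- **Missingness is limited.** Deaths are scored under the primary outcome section, so they are outside this gap. Assessment is offered after the intervention is declined, and a second carer may complete GAS. These provisions help, but the last two are worded around leaving the intervention and so bear mainly on one arm.
- **The size is assumed.** It is, and equal dependence in both arms gives no bias.

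**Conclusion.** The point holds. The plan fixes a 12-month-only primary model and commits to a missing-data analysis that cannot see progress after randomisation, although a rating of that progress is scheduled for every dyad. The potential bias is modest: about 0.02 to 0.08 SD on a 0.5 SD target if poorer progressors leave one arm only, larger if dependence runs in opposite directions, and zero if it is equal.

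These sizes rest on an assumed correlation, an assumed gap between leavers and stayers, and loss at the 15% ceiling. The documents support none of these beyond the 15%. The full correction in the simulation also assumes that every leaver was rated at 6 months and that, given arm and 6-month score, dropout is unrelated to the 12-month score. The change is worth making because it is cheap and removes a foreseeable weakness; the documents do not show that the result will be wrong.

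**What to change.** In the analysis plan, before final data are available, commit to one of the following:

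1. **Joint model.** Analyse 6- and 12-month GAS together, with arm-by-time effects, an unstructured within-dyad covariance and the same therapist and site terms. Report the 12-month contrast as the primary result.
2. **Multiple imputation.** Keep the 12-month model and commit to imputation carried out separately by arm, with 6-month GAS as an auxiliary variable and not as a covariate in the treatment-effect model.

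Do the same for the continuous secondary outcomes. The adjustment for baseline predictors of missingness can stay as a supplement.

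The cost is a slightly more complex model and some wording; no new data and no change to the 297 dyads. The limit is that dyads lost before 6 months gain nothing, so missing counts should be reported by arm, separating those lost before and after the 6-month rating.

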#### Plans to give access to the full protocol, participant level-data, and statistical code {31c}

The trial protocol is available via the ISRCTN registry (ISRCTN11425138). Participant-level data will be managed by PRIMENT CTU and made available on request, based on the SOP. The statistical code will be disclosed by the senior statistician on receipt of a reasonable request.

### Oversight and monitoring

#### Composition of the coordinating centre and trial steering committee {5d}

The study will be overseen by clinical academics based at UCL Division of Psychiatry, PRIMENT CTU, a Programme Management Group (PMG), and independent trial steering committee (TSC). The PMG will include the chief investigator, co-investigators, the trial manager, trial statisticians, health economists, researchers, research network volunteers, and representatives from PRIMENT CTU. The PMG will be responsible for overseeing the trial. The TSC will be chaired by an independent clinical academic and will include an independent statistician and three research network volunteers, two PRIMENT CTU representatives alongside the CI, trial manager, and lead statistician for the study.

#### Composition of the data monitoring committee, its role and reporting structure {21a}

The DMEC is combined with the PMG, as agreed with PRIMENT CTU and the funder, because this is a low risk intervention trial.

#### Adverse event reporting and harms {22}

Any serious adverse events (SAEs) which are classified as related and unexpected will be reported to the chief investigator (CI) of the study in the first instance and the local principal investigator (PI)/participant’s GP/clinician. The TSC and PRIMENT CTU will review serious adverse events and events will be reported to the research ethics committee (REC) that approved the trial. All parties will be kept informed of serious adverse events via the trial manager. All SAEs will be recorded on the online database hosted by Sealed Envelope. The CI/PI or designated researcher will complete the SAE form and the form will be preferably emailed to PRIMENT CTU within 24 h of becoming aware of the event by the trial manager. The CI or PI will respond to any SAE queries raised by the sponsor as soon as possible.

#### Frequency and plans for auditing trial conduct {23}

The PMG will meet approximately twice a year. Its remit is to review recruitment figures, serious adverse events and substantial amendments to the protocol prior to submission to the REC. The study team will also consult the independent TSC twice a year to provide overall supervision of the trial. The TSC will review the recommendations of the PMG and, on consideration of this information, recommend any appropriate amendments/actions for the trial as necessary.

#### Plans for communicating important protocol amendments to relevant parties (e.g. trial participants, ethical committees) {25}

The trial manager will submit any protocol amendments to the sponsor for approval prior to submission to the REC. The trial manager will communicate amended and approved documentation to all researchers and research sites involved in the study and will update the trial registry with any additional or revised study information.

### Dissemination plans {31a}

We will work with our PPI group in developing our dissemination plans. Findings will be disseminated in a peer reviewed journal, at an international conference, and will be presented in appropriate local forums for health and social care professionals. Participants who have indicated they are interested in the results will be sent a lay summary of the findings by post or email.

## Discussion

To our knowledge, this is the first manualised intervention tailored to personalised goals of people living with dementia and their families, delivered by facilitators without clinical training. GAS, our selected primary outcome, can detect clinically meaningful outcomes [16], through measuring the extent to which individual patients or their families meet the goals that they set. Our approach of using GAS as both an outcome measure and to directly inform a non-pharmacological intervention for people living with dementia and their families, and to train non-clinical staff to set goals, is novel.

GAS can serve as a co-intervention, where setting a goal is key to achieving it [41]. For this reason, various means of modifying the process have been developed, including standardised, protocol-specific training [42] and semi-standardised menus [43], which we will employ. Limitations of GAS include the sometimes cumbersome process of setting and adjudicating individual goals [44] and a current lack of good quality validity studies [45]. While there will be heterogeneity in goals set, this is remedied through its employment in a randomised controlled trial, with masking of who has received the intervention, and with patient assignments to treatment arms occurring only after goals have been set [33].

There have been operational issues associated with the shift to remote delivery. We worked collaboratively with [name]’s team to ensure the goals we set using GAS were SMART, including being achievable and relevant to the uncertain COVID and post-COVID world. A particular concern was to avoid goals where achievement would be dependent on lifting of lockdown restrictions. Researchers received additional training in delivering remote interventions and supporting participants to set up video calls. We have considered carefully how to support researchers delivering the intervention from their own homes and to ensure the boundaries of sessions are maintained in this new format; regular clinical supervision has been key to addressing this. Session content has also been adapted, as discussed in the ‘Introduction’ section. Remote delivery means that the format of our intervention is further from that delivered in our feasibility trial than originally intended. In the light of COVID-19, there have been considerable recent efforts to explore how remote and face-to-face psychological intervention delivery may differ in their impacts; one review reported minimal to no difference between telephone and face-to-face therapy in terms of the nature of the interaction between the therapist and client [46], but more information will emerge as we assimilate knowledge from the sudden shift to remote delivery in spring 2020. The usual care received by all participants will also have shifted to mainly remote delivery during lockdown, and social care receipt will have reduced. While we could not have envisaged the huge shifts to telecare the pandemic has enforced, NIDUS-family was always intended as a pragmatic intervention, comparing tailored, structured additional support sessions to usual care. The pragmatic and flexible nature of the intervention has enabled us to continue evaluating it throughout this period.

## Trial status

Protocol version number 3: 6 April 2020. The first participant dyad was recruited on 3 April 2020. Recruitment will cease in February 2022.

## Abbreviations

b-DAS: Brief Dimensional Apathy Scale
CarerQol: Care-Related Quality of Life Instrument
CI: Chief investigator
CRF: Case report form
CRN: Clinical Research Network
CSRI: Client Services Receipt Inventory
CTU: Clinical Trials Unit
DADS: Disability Assessment for Dementia Scale
DMEC: Data Monitoring and Ethics Committee
GAS: Goal Attainment Scaling
HADS: Hospital Anxiety and Depression Scale
ICC: Intracluster correlation coefficient
ISRCTN: International Standard Randomised Controlled Trials Number
NIDUS: New Interventions for Independence in Dementia Study
PI: Principal investigator
PIS: Participant information sheet
PMG: Programme Management Group
PPI: Patient and public involvement
QALY: Quality-adjusted life year
REC: Research Ethics Committee
SAE: Serious adverse event
SMART: Specific, Measurable, Achievable, Realistic and Timely
STATA: Software for Statistics and Data Science
TSC: Trial steering committee
UCL: University College London
UoB: University of Bradford
